## Data management

Data is collected electronically and questionnaires in paper format. The quality of data collection and data entry is maximized through training of field staff in standardised methodology and missing data checks during the study. For data entry, a 5% sample will be validated by another member of the research team to monitor error rates. The data will be inputted into Microsoft Excel programme (Microsoft, Redmond, WA, USA) and exported to SPSS V.27 (IBM SPSS Statistics for Windows, IBM Corporation, Armonk, NY) and GraphPad Prism V.9 (GraphPad Software, La Jolla, CA, USA) for analysis. Verified and validated data will be stored via the cloud on a secure, highly fault-tolerant, storage area network server at NMS, FCM, UNL. All data will be accessible only to the research team. The anonymized participant-level dataset and statistical codes will be made available upon reasonable request. The folders that contain all anonymized research data will be preserved for at least 10 years.

## Statistical analysis

Statistical analysis will be performed using SPSS V.27 (IBM SPSS Statistics for Windows, IBM Corporation, Armonk, NY) and GraphPad Prism V.9 (GraphPad Software, La Jolla, CA, USA).

Participants with low compliance as defined by taking less than 80% of the pills provided by the research team and those lost to follow-up will be excluded from the per-protocol analysis but included in the intention-to-treat analysis. In addition, all participants are strongly advised not to take any probiotic supplements. Participants are asked at each visit about the intake of antibiotics and probiotics supplements, in case of intake in any period of the trial after starting the intervention, participants will also be excluded from the per-protocol analysis but will be included in the intention-to-treat analysis. In case of lost to follow-up, available data from electronic medical records will be collected.

The Kolmogorov–Smirnov test will be used to test the normality of the distribution. Descriptive statistics will be performed, and data will be presented as mean ± standard error of mean (SEM) (for normally distributed continuous variables) or median [interquartile range (IQR)] for nonnormal quantitative data and frequency (percentage) for categorical data. Data will be evaluated for the presence of outliers, violations of normality, and missing data. Major violations of normality will be corrected with an appropriate transformation procedure (i.e. logarithmic transformation for positively skewed and exponential function for negatively skewed data). To analyse the differences in the continuous variables between the intervention and placebo groups, different tests will be used depending on the data distribution. Paired samples *t*-test will be used for normal data and Wilcoxon signed rank test for non-normal data. Categorical variables will be analysed by *X*^2^ test. Correlations between outcomes will be evaluated by Pearson’s chi-square and Spearman correlation test. Relative risks and weighted mean differences will be employed to calculate the dichotomous and continuous data, respectively.

Some prespecified subgroup analysis will be done based on some confounding variables such as age, gender, diagnosis of type 2 diabetes, etc., for detecting heterogeneity in intervention efficacy across the strata of mentioned variables. However, these subsamples will be compared to the main dependent variables at baseline. Potential confounding variables will be evaluated in each model. Regression models will be used to predict which factors at baseline most contribute to excess weight loss 1 year after the surgery.

Differences will be considered statistically significant when *p* < 0.05. Effect sizes (Cohen d test) will also be assessed to decide whether a clinically relevant effect is found (|d|> 0.50 indicates a medium effect size and |d|> 0.80 indicates a large effect size).

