### Gastrointestinal quality of life

Previous studies have shown that the administration of probiotics may improve symptomatic gastrointestinal episodes after gastric bypass surgeries and improve quality of life [26, 27]. Therefore, to assess the gastrointestinal quality of life before and after intervention participants fill out a self-reported questionnaire [Gastrointestinal Quality of Life Index (GIQLI)] at all visits. GIQLI questionnaire includes 36 items divided between five domains: symptoms, physical dysfunction, emotional dysfunctions, social dysfunction, and effect of treatment. The total score is computed as the sum of the response option to each of the 36 items, ranging from 0 (least desirable option) to 4 points (most desirable option). The total score is the sum of item points and ranges from 0 to 144, with higher scores indicating more favourable conditions [28].

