## Sample size

Sample size calculations have considered the outcomes: percentage of excess weight loss and fasting blood glucose levels. Based on previous studies with a population similar to this study, the assumed standard deviation was 10.70 for percentage of excess weight loss [37] and 14.00 mg/dL for fasting blood glucose [38]. To detect a difference of 10.48% [39] in excess weight loss and 11.30 mg/dL [40] in fasting glucose between the intervention and placebo group after 1 year of follow-up, it was determined that 44 participants are required to allow for an 80% power and 95% confidence level. Compensating for possible attrition, 30% additional samples will be recruited, representing a total of 58 participants (29 in each arm — probiotic group and placebo group). Considering that Hospital CUF Tejo receives around 80 patients each year to be submitted to bariatric surgery, of these around 70% are Roux-en-Y gastric bypass, assuming that 29% of the subjects will not be eligible to participate [39], it is anticipated that it will take approximately 18 months to recruit this sample size.

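### The exponential transformation for negatively skewed data has no stated scale or check, is chosen after a normality test, and can cost much power on continuous excess weight loss

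*Protocol article*

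**What the plan says.** All of the rule stands in one paragraph of the protocol article, under Statistical analysis.

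- The trigger: "The Kolmogorov–Smirnov test will be used to test the normality of the distribution". The plain and Lilliefors forms are not distinguished.
- The correction: "Major violations of normality will be corrected with an appropriate transformation procedure", spelled out as a "logarithmic transformation for positively skewed and exponential function for negatively skewed data".
- The alternative route: a t-test for normal data and a "Wilcoxon signed rank test for non-normal data".

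The paragraph does not give the scale on which the exponential is taken. It does not ask for normality to be checked again afterwards, and it does not set the order of transformation and rank test.

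Two continuous variables on wide scales fall under the rule. %EWL is computed as a ratio times 100 (Anthropometry and body composition), and under Sample size "the assumed standard deviation was 10.70 for percentage of excess weight loss". The gastrointestinal quality-of-life total (GIQLI) "ranges from 0 to 144".

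**The concern.** A logarithm is insensitive to the unit: changing the unit only adds a constant. An exponential is not. On a variable measured in tens of units, exp(x) spans many orders of magnitude, the group mean becomes essentially its largest value or two, and mild negative skew turns into extreme positive skew. A t-test on such values has little power.

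The second weakness is the choice itself. The same non-normal variable may be analysed raw, transformed or by ranks, depending on a test run on the trial data and on what the analyst counts as a major violation. The article does not settle which result is the reported one.

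The stakes are the continuous outcomes. %EWL is the subject of the first primary aim (Study objectives) and a sample-size variable; GIQLI is a secondary aim.

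**Working it through.** **Inputs from the article.** %EWL: SD 10.70, difference 10.48. The Sample size section gives 44 evaluable participants, so 22 per arm at 1:1. Alpha 0.05, taken as two-sided.

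**Inputs assumed.** Control mean 65 or 70 points, and negative skewness from -0.5 to -2 generated as a reflected gamma distribution. The article gives neither.

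**The plan's own figure.** The standardised difference is d = 10.48/10.70 = 0.98. For 80% power the normal approximation gives n per arm = 2(1.96 + 0.84)²/0.98² ≈ 16.4, rounded up to 17, so 34 in total (36 with the t distribution). Fasting glucose, with d = 11.30/14.00 = 0.81, needs 50 (52 with t). The stated 44 does not follow from either; that is a separate matter. For this point, what counts is the power for %EWL at 22 per arm: d√(22/2) = 0.98 × 3.317 ≈ 3.25, and Φ(3.25 − 1.96) ≈ 0.90, or 0.89 with t. The simulations give about 0.88 on untransformed data, in line with this.

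**Effect of the unit.** One SD of %EWL multiplies exp(x) by e^10.7 ≈ 44,000. At skewness -1 the largest of 22 values carries a median of about 79% of its group's total.

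**Simulated power, %EWL, 22 per arm, 10,000 trials per setting, unpaired tests**

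| Skewness | -0.5 | -1 | -1.4 | -2 |
|---|---|---|---|---|
| t-test, untransformed | 0.88 | 0.88 | 0.88 | 0.88 |
| Rank-sum | 0.88 | 0.91 | 0.94 | 0.97 |
| exp(x) in points, then t-test every time | 0.01 | 0.03 | 0.11 | 0.62 |
| exp(x/SD), then t-test | 0.89 | 0.97 | 0.99 | 1.00 |
| exp(x/100), then t-test | 0.90 | 0.91 | 0.92 | 0.92 |

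With Welch's test the third row is about 0.5%, 2%, 11–12% (at skewness -1.5) and 56–57% (at -2).

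**The whole rule.** The transformation is applied only when the normality test on pooled residuals rejects; otherwise the raw data go to a t-test.

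| Skewness | -0.5 | -1 | -1.4 | -2 |
|---|---|---|---|---|
| Lilliefors: share triggered | 12% | 34% | 60% | 89% |
| Lilliefors: power, no recheck | 0.79 | 0.61 | 0.44 | 0.66 |
| Plain test: share triggered | 0.2% | 1% | 5% | 23% |
| Plain test: power, no recheck | 0.88 | 0.88 | 0.85 | 0.84 |
| Lilliefors, recheck, then unpaired rank test | 0.89 | 0.90 | 0.93 | 0.97 |

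With Welch's test and skewness -1.5 included, the no-recheck ranges are about 40–79% (Lilliefors) and 82–89% (plain). In every triggered data set the values were still non-normal after exp(x) in raw points.

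**GIQLI.** The article gives no mean, SD or effect. With an assumed SD of 15, a 13-point effect and scores capped at 144, power after exp(x) and a t-test every time is about 0–4% at a control mean of 100–105, 27–41% at 115 and 56–94% at 120. With mean 110, SD 18 and d = 0.98 it is 53–70%, against 86–88% untransformed. The result depends mainly on how many scores reach the ceiling.

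**The case against.** The strongest reply is that the article never says exp(x) is taken in raw points, nor that a t-test follows whatever the transformed data look like. It limits the step to major violations and asks for an appropriate procedure. An increasing convex function is the right direction for negative skew, and exp(x/SD) or exp(x/100) loses nothing in these simulations. The same paragraph sends non-normal data to a rank test, and a rank-sum test is unchanged by any increasing transformation. All of this stands, and it limits the claim to what the rule can do under one reading. It does not rescue the rule: at skewness -1, power runs from about 2–3% to 97% on a scale the text leaves open. If a rank-sum test follows, the transformation is pointless. The rank test named is also a paired one, which does not fit two independent arms; that is a separate matter, and the simulations used unpaired tests.

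A reader might also infer that a weak normality test makes the loss worse. It works the other way. The plain test rarely fires, so the harmful step is rarely taken; the larger loss comes with the more sensitive Lilliefors form. What remains is that a gate which misses real skew, and applies a poor correction when it fires, serves no purpose.

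Finally, an article may leave detail to a full plan. The exponential, however, is a rule stated here, not a detail omitted.

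**Conclusion.** The point holds in a limited form. The rule is badly fixed: it depends on an unstated unit, has no check, and leaves the choice between raw, transformed and rank analyses until the data are seen. In raw points with a t-test every time, %EWL power falls from about 88% to about 1–12% at skewness -0.5 to -1.5, and to about 56–62% at -2. Over the whole rule without a recheck it is about 40–79% (Lilliefors) or 82–89% (plain).

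It may be tempting to read this as near-certain loss of the trial's power. The documents do not support that. Nothing in the article says that %EWL or GIQLI is negatively skewed, and the means and skewness used here are assumptions. The primary outcomes, as defined under Primary outcomes, are counts of participants (at least 50% of excess weight lost; HbA1c below 5.7%) that go to a chi-square test, so the rule does not touch them. Nor can a general figure be given for GIQLI, because the size of any loss turns on inputs the article does not state. This should be corrected, but it does not undermine the primary comparison.

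**What to change.** Delete the exponential transformation and the Kolmogorov–Smirnov gate. For each continuous outcome, name one unpaired between-group analysis in advance:

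- For %EWL, HbA1c and GIQLI, the mean difference on the original scale from a linear model adjusted for the baseline value. %EWL is zero at baseline by its formula, so adjust for baseline weight or BMI instead.
- For right-skewed biomarkers, the same model on the log scale.
- A rank-sum test as a sensitivity analysis.

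The cost is about two sentences in the analysis section, with no new data and no change to the sample size. It should be done before the group codes are attached to the data.

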### Intervention, compliance, and adverse effects

Participants enrolled in the trial are randomly assigned to receive either probiotic or placebo. The probiotic or placebo is orally taken, twice a day, with one glass of water, approximately 5 min before both breakfast and lunch, for 90 days, between 3 and 6 months after bariatric surgery. Two capsules of the probiotic contain 5 × 10^7^ CFU of *Hafnia alvei* HA4597™, 5 mg of zinc and 20 μg of chromium. The capsules are gastro-resistant which allows the ingredients to resist stomach acidity. A placebo is used as a comparator to determine if the probiotic effect is directly related with the strain (i.e. *Hafnia alvei*). The placebo product is indistinguishable in colour, smell, and taste from the active formulation, and has the same composition but without the live bacteria.

To improve compliance, participants will receive a message every 2 weeks and a call approximately 45 days after starting the intervention to reinforce the intake of the capsules and to register any missing intake on the calendar provided by the research team.

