### Sample collection and follow-up

Eligible participants are assessed five times during the trial: at baseline (visit 1), 3 months (visit 2), 6 months (visit 3), 9 months (visit 4), and 12 months (visit 5) after bariatric surgery. Intervention (i.e. intake of probiotic or placebo) is administered 3 months after the surgery. All data is collected at Hospital CUF Tejo and the specific assessments carried out at each timepoint are identified in Table 1.

Before each visit, participants are contacted and reminded of their follow-up visits and necessary preparations via e-mails and text messages. Participants are asked to prepare for all the visits by following the instructions:Fasting for 10–12 h (allowed to drink water 4 h before the visit)Having a last meal similar to their usual habitsAvoiding alcohol and caffeine intake on the previous dayAvoiding vigorous physical exercise on the previous day

At baseline, participants respond to a questionnaire to provide sociodemographic characteristics, clinical history, and lifestyle practices. Information regarding changes in medication, supplementation and physical activity are continuously gathered throughout the trial through the electronic patient record.

At all visits, a venous blood sample is collected by a nurse/phlebotomist into sterile serum separator tubes and K_2_EDTA tubes. Subsequently, blood samples are centrifuged at 3000 rpm for 10 min at 4 °C, and aliquoted. For incretin hormones aliquot, DPP-IV inhibitor is added to plasma sample to a final concentration of 10 μL/mL of blood. Participants are also instructed to collect their own faecal samples in sterile tubes with RNAlater, provided by the research team. Subjects describe their stool frequency and consistency of evacuation using the Bristol stool scale [23]. All biological samples are stored at − 20 °C (faecal samples) or − 80 °C (plasma and serum samples) until further analysis.

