### Anthropometry and body composition

Height is measured to the nearest 0.1 cm with a wall stadiometer (SECA®, Hamburg, Germany), following the Directorate-General for Health protocol [24]. Participants remove their clothes, socks, and any metal objects prior to measurement of body weight and body composition (including percentage of fat mass, fat mass, fat-free mass and skeletal muscle mass) by tetrapolar bioimpedance (Inbody®, model 770, Seoul, Korea). Body mass index is also obtained by the device report and percentage of excess weight loss is calculated as: $$\frac{\mathrm{baseline\,weight}\left(\mathrm{kg}\right)-\mathrm{follow\,}-\mathrm{\,up\,weight}\,(kg)}{\mathrm{baseline\,weight}\left(\mathrm{kg}\right)-\mathrm{ideal\,weight\,for\,BMI\,}25\mathrm{\,kg}/\mathrm m^2}\times100$$ [25]. Weight and body composition is measured at all visits.

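### Continuous outcomes measured at five visits are compared by a single distribution-chosen test, which cannot include a participant who has no study or record value at the tested visit

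*Protocol article*

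**What the plan says.** All references are to the protocol article.

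- **Method.** Statistical analysis: "To analyse the differences in the continuous variables between the intervention and placebo groups, different tests will be used depending on the data distribution". The tests named are a paired t-test for normal data and the "Wilcoxon signed rank test for non-normal data". The only regression described, at the end of that section, looks for baseline predictors of weight loss; it is not the arm comparison.
- **Visits.** Sample collection and follow-up: "Eligible participants are assessed five times during the trial", at baseline and months 3, 6, 9 and 12. Anthropometry and body composition: "Weight and body composition is measured at all visits". The Secondary outcomes section schedules the metabolic, inflammatory, microbiota and quality-of-life outcomes repeatedly as well.
- **Treatment period.** Capsules are taken "for 90 days, between 3 and 6 months after bariatric surgery". Baseline and month 3 are therefore pre-treatment values; months 6, 9 and 12 follow the start of treatment.
- **Attrition.** Sample size: "44 participants are required to allow for an 80% power and 95% confidence level", and then "Compensating for possible attrition, 30% additional samples will be recruited, representing a total of 58 participants".
- **Loss to follow-up.** Statistical analysis keeps these participants in the intention-to-treat analysis, drops them from the per-protocol analysis, and says that whatever their electronic records hold will be collected. Data will be examined for missingness, but no method for handling it is named.

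**The concern.** A test that takes one month-12 result per person has no use for the month-6 and month-9 results of someone without a month-12 result. In a trial of 58 that wastes information that has already been collected. It also leaves the intention-to-treat promise without a mechanism for anyone whose record holds nothing for that visit.

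Bias is the more important risk. If participants who are doing worse tend to stop attending, those left at month 12 are a selected group. When the same tendency acts in both arms, selection is heavier in the arm that does worse, and the difference shrinks toward zero. A likelihood-based longitudinal model removes this bias when dropout depends only on values already observed.

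The outcomes touched include percentage excess weight loss (%EWL) and fasting glucose, on which the trial is sized, and HbA1c. This is a method that the article states, not a detail it leaves to another document.

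**Working it through.** **Inputs from the article.** 44 required and 58 recruited, 1:1 (22 and 29 per arm); %EWL difference 10.48, SD 10.70; fasting glucose difference 11.30 mg/dL, SD 14.00 mg/dL.

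**Assumed, not in the article.** Correlation ρ between an earlier value and month 12; when dropout occurs; how it relates to response; how the effect builds up; two-sided 5% level.

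**Step 1: the attrition figure.** 44 × 1.30 = 57.2, rounded up to an even 58, which reproduces the article. The implied allowance is (58 − 44)/58 = 14/58 = 24.1%.

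**Step 2: precision at month 12.** Take m observed per arm at month 12 and N per arm with an earlier post-start value. The variance of an arm mean is σ²/m for completers only and approximately σ²[1 − ρ²(1 − m/N)]/m under a likelihood model. The ratio is 1/[1 − ρ²(1 − m/N)].

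- Every dropout has an earlier value (m = 22, N = 29, 1 − m/N = 0.241). For ρ = 0.5: 1/(1 − 0.25 × 0.241) = 1.06. For ρ = 0.9: 1/(1 − 0.81 × 0.241) = 1.24. Effective n per arm is 22 × ratio = 23.4 to 27.3.
- Half of the dropouts have one (N = 25.5, 1 − m/N = 0.137). The ratios are 1.04 and 1.13; effective n is 22.8 to 24.8.

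**Step 3: power,** Φ[d/(SD√(2/n)) − 1.96].

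- Completers, n = 22. %EWL: 10.48/(10.70 × 0.3015) = 3.25, power 90.1%. Glucose: 11.30/(14.00 × 0.3015) = 2.68, power 76.3%.
- Model, every dropout with an earlier value: %EWL 91.8 to 95.2%, glucose 78.9 to 84.7%.
- Model, half of the dropouts: glucose 77.8 to 81.0%.

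**Step 4: sensitivity to the dropout pattern.** Simulated trials used 29 per arm, the %EWL figures, and correlations of 0.6 / 0.8 / 0.9 between adjacent visits. The extra-variance column has about 24% missing at random, except in the last row. In the estimate column, dropout odds rise 2.7-fold per SD of poorer last result, with about 30% missing in the first row. Ranges cover repeat runs.

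| Assumption | Extra variance, completers only | Completers' estimate (true 10.48) |
|---|---|---|
| No loss before month 6, full effect from month 6 | 5–6% / 15–16% / 19–24% | 9.5–9.7 / 9.1–9.2 / 8.9–9.0 |
| Effect builds linearly to month 12 | not reported | 10.0 / 9.8 / 9.7 |
| About half of the loss before month 6 | 3% / 8% / 10% | not reported |
| Both changes | about 0–3% | 10.0–10.2 |

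In the first row the likelihood estimate stayed at 10.4 to 10.6. Across the rows the completers' shortfall runs from 10.48 − 10.2 = 0.3 to 10.48 − 8.9 = 1.6 points, about 3% to 15% of the assumed difference.

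**The case against.** A reader might infer that everyone who misses month 12 is discarded and that the intention-to-treat analysis is simply a completers' analysis. The article does not support that. It commits to retrieving record data, post-surgical appointments follow the hospital's own protocol, and HbA1c is listed among routine laboratory parameters, so weights and HbA1c may well be recovered. What remains is the participant with no retrievable value. That is likeliest for the GIQLI questionnaire, microbiota, metabolite and ELISA outcomes, which the trial generates itself.

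A reader might also infer that the primary outcomes are affected. As the Primary outcomes section defines them, they are counts of responders at one year, which fall under the chi-square test. A model for continuous outcomes leaves them and their missing data unchanged. The point does reach %EWL and HbA1c as worded in the primary aims.

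Third, 24% is an allowance for possible attrition, not a forecast. Allocation takes place just before capsules start, so part of it may cover losses before allocation, which do not bias the arm contrast.

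Fourth, the larger figures above need nobody lost before month 6 and the full effect already present then. With both relaxed, little is left. This objection stands, and it limits the size of the point.

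Finally, longitudinal modelling and imputation are often left to a fuller document. That would answer silence, but here a test is named, and it fits the design poorly.

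**Conclusion.** The point holds in limited form. The stated method uses one comparison per continuous outcome, ignores the other post-start visits, and gives no route into the intention-to-treat comparison for a participant without a study or record value at the tested visit. The cost is modest: roughly 0 to 24% extra variance, and a month-12 difference that is biased if dropout depends on earlier response. The simulated shortfall of 0.3 to 1.6 %EWL points only illustrates that bias; the article gives nothing from which its actual size could be derived. The gain in precision matters most for fasting glucose, where 22 per arm gives 76.3% power against the stated 80%.

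The change is worth making because it is cheap, not because the existing comparison is invalid on this ground. That the named tests are paired tests, although the arms are independent, is a separate and more serious error. Correcting it to unpaired tests would leave this point in place.

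**What to change.** For each continuous outcome, fit one likelihood-based mixed model for repeated measures in all randomised participants. Include arm, visit, arm-by-visit, the baseline and month-3 values, and the HbA1c randomisation stratum, with an unstructured covariance. Report the month-12 contrast with its 95% CI. Enter retrieved record values as observations.

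Two details:

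- Put the pre-treatment values in the response vector with means common to both arms. As covariates only, they leave a participant lost before month 6 contributing nothing.
- %EWL at baseline is zero for everyone by its formula, so use baseline weight there; month-3 %EWL is the informative pre-treatment value.

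Keep an unpaired two-sample test at month 12 as a check. The cost is a change of wording; SPSS V.27, already named, fits the model. The downsides are a somewhat more complex method and a missing-at-random assumption that must be stated. The responder primary outcomes need their own provision for missing values.

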## Methods

### Trial design and study setting

This one-year, triple-blinded, blocked-randomized, parallel-group, placebo-controlled clinical trial is designed to determine the effect of *Hafnia alvei* HA4597™ supplementation on weight loss and glycaemic control 1 year after bariatric surgery. The trial is being conducted at Hospital CUF Tejo (Lisboa, Portugal) and samples and data will be analysed at Faculdade de Ciências Médicas, NOVA Medical School, NMS, FCM, Universidade NOVA de Lisboa (Lisboa, Portugal) (NMS, FCM, UNL). The design of the proposed study protocol is shown in Fig. 1.

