#### Randomization, allocation, and blinding

Eligible participants are randomized using block randomization in a 1:1 ratio to either the probiotic or the placebo group. Blocked randomization is stratified according to HbA1c levels obtained at first visit (baseline), following American Diabetes Association guidelines for pre-diabetes and diabetes diagnosis (normal: < 5.7%; pre-diabetes: 5.7–6.4%; diabetes: ≥ 6.5%) [16]. The randomization is performed using the National Cancer Institute clinical trial randomization tool (https://ctrandomization.cancer.gov/). A minimisation method is used on the allocation process to ensure the required balance across the intervention and control groups. Results are sent to an independent researcher responsible for allocation that is not involved in the recruitment nor in the delivery of the intervention. The allocation is performed right before the beginning of the intervention of each group of randomized participants (in blocks), sending the results to a local researcher in a pre-printed Excel worksheet (Microsoft, Redmond, WA, USA). Randomization and allocation of participants are carried out by different researchers.

The study products are packaged and blinded by an outsourced pharmacy. The package appearance of both products is identical; thus, participants and care providers will be blinded to the intervention. All researchers involved in the trial are also blinded to the intervention allocation until the trial is completed. At the end of the study, researchers performing the statistical analysis will divide the participants into the coded groups and will be unaware regarding the intervention allocation. A member of the research group that is not involved in the study nor participates in the investigation meetings is responsible to keep the sealed envelopes with the allocation of each code in a locked drawer. After performing the analyses, the sealed envelope will be opened by the coordinating and principal investigators.

Unblinding will be needed in case of medical event emergencies or serious medical conditions that may occur during the trial whereby the physician needs to know which treatment they have been receiving. However, given the nature of the intervention and placebo, it is unlikely to occur.

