### Primary outcomes

The primary outcomes are the differences in the number of subjects that will lose at least 50% of excess weight, as well as the number of subjects that will have glycated haemoglobin levels lower than 5.7%, between the probiotic and placebo groups, 1 year after the surgery. The rationale behind the primary outcomes is based on previous studies that have described the effect of *Hafnia alvei* HA4597™. In the preclinical study conducted by Legrand et al. [14], the effect of *Hafnia alvei* HA4597™ supplementation was assessed in two models of obesity, in leptin deficiency *ob/ob* mice and high-fat diet (HFD)-fed obese and overweight mice. Results showed that in both models’ body weight gain was significantly lower by the end of the study (50.1% *ob/ob* and 38.1% HFD), as well as fat gain (38.3% *ob/ob* and 51.9% HFD) [14]. In addition, loss of lean mass was 126.8% lower and food intake reduced 20.8% in the *ob/ob* mice [14]. A second trial was conducted by Lucas et al. [11] using a mice model of obesity characterized by a combination of a HFD-fed obese and a genetic *ob/ob* mice which closely represents the hyperphagia and diet-induced obesity in humans (compulsive eating behaviour combined with hypercaloric diet and functional leptin resistance). The authors observed that *Hafnia alvei* HA4597™ supplementation resulted in 58.1% lower body weight gain, decreased food intake and fat mass gain, and increased lean mass preservation, resulting in an improved lean/fat mass ratio [11]. Moreover, *Hafnia alvei* HA4597™ treatment also improved metabolic outcomes, including glycemia. Basal glucose levels decreased by 1.5-fold compared to standard diet HFD-fed controls [11]. Afterwards, the efficacy of *Hafnia alvei* HA4597™ supplementation was tested in humans [15]. A randomized, placebo-controlled, double-blind trial evaluated the effect of this probiotic (5 × 10^7^ CFU of *Hafnia alvei* HA4597™) on 236 overweight men and women that were following a low-calorie diet [15]. After 12 weeks, significantly more subjects (+ 51%) lost at least 4% of their initial weight comparing to placebo [15]. Furthermore, compared to placebo, subjects in the treatment group had a significant reduction in hip circumference and glycemia, and increased feeling of fullness, which was assessed by a visual analogue scale [15].

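### Paired tests are named for the between-arm comparison of continuous outcomes, although the two arms are independent and unmatched

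*Protocol article*

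**What the plan says.** The design is set out under Trial design and study setting: "This one-year, triple-blinded, blocked-randomized, parallel-group, placebo-controlled clinical trial". Under Randomization, allocation, and blinding: "Eligible participants are randomized using block randomization in a 1:1 ratio to either the probiotic or the placebo group". Blocks are stratified by baseline HbA1c category. Matching and crossover are not described anywhere.

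The Statistical analysis section gives the purpose of the tests in one sentence, "To analyse the differences in the continuous variables between the intervention and placebo groups, different tests will be used depending on the data distribution", and names them in the next, "Paired samples *t*-test will be used for normal data and Wilcoxon signed rank test for non-normal data". It then turns to categorical data: "Categorical variables will be analysed by *X*^2^ test". It also mentions relative risks and weighted mean differences, and later Cohen's d, as effect measures. The significance rule is "Differences will be considered statistically significant when *p* < 0.05".

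The article names no independent-samples t-test, Mann-Whitney test or between-arm model. Its regression models are for finding baseline factors that predict excess weight loss.

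**The concern.** A paired test needs a real link between each value in one sample and one value in the other. Here there is none. An analyst following the text has three options:

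- pair rows arbitrarily, and get a p-value that changes when the file is re-sorted;
- drop participants until the arms are the same size;
- run the tests before and after within each arm, which leaves the randomised contrast on continuous outcomes without a hypothesis test.

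The outcomes exposed are percentage of excess weight loss and HbA1c as worded in the primary aims, excess weight loss and fasting glucose as used in the sample size, and the continuous secondary outcomes.

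**Working it through.** **Inputs.** From Sample size: "the assumed standard deviation was 10.70 for percentage of excess weight loss [37] and 14.00 mg/dL for fasting blood glucose"; target differences 10.48 points and 11.30 mg/dL; 44 evaluable (22 per arm); 58 recruited (29 per arm). Two-sided 0.05 is assumed, because sidedness is not stated.

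Standardised differences: 10.48/10.70 = 0.98 for excess weight loss; 11.30/14.00 = 0.81 for glucose.

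**The plan's own figure.** With an independent-samples t-test at 80% power, excess weight loss needs 36 in total and glucose 52. The stated 44 is not reproduced for either. The attrition step does reproduce: 44 × 1.3 = 57.2, rounded up to 58. The mismatch in 44 is a separate matter and nothing below depends on it beyond using 22 per arm.

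**Why row order matters.** Re-pairing leaves the mean difference unchanged but changes the SD of the paired differences:

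s_d² = s₁² + s₂² − 2·r·s₁·s₂,

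where r is the accidental correlation created by the pairing. With equal SDs, t_paired = t_independent / √(1 − r).

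Example with 22 per arm, both SDs 14 and mean difference 8.5:

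- Independent test: t = 8.5 / (14 × √(2/22)) = 2.01 on 42 df, p = 0.050.
- Paired test: 2.01/√(1 − r) on 21 df, critical value 2.08. It is significant whenever r exceeds 1 − (2.01/2.08)², which is about 0.06.
- Over 20,000 random re-pairings of one such data set, p ran from 0.00003 to 0.14, and 40% of pairings fell below 0.05.

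**How often the conclusion depends on the pairing** (simulated data sets, 22 per arm, 200 random pairings each):

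| Standardised difference | Central 95% of p-values crosses 0.05 | Any of the 200 pairings differs |
|---|---|---|
| 0.8 (near glucose) | 28% | 37% |
| 0.98 (excess weight loss) | 17% | 23% |

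**Error rate and power under random pairing** (22 per arm):

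| | Independent t-test | Paired t-test, random pairs |
|---|---|---|
| Type I error | 4.8–4.9% | 4.9–5.0% |
| Power, excess weight loss | 88.7% | 87.2% |
| Power, glucose | 74.4% | 72.3% |

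The power loss is 88.7 − 87.2 = 1.5 points and 74.4 − 72.3 = 2.1 points, and comes from having 21 rather than 42 degrees of freedom.

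**Can the test run at all?** A paired routine given 22 and 21 values returns an error. Going from 58 to 44 is a loss of 14/58 = 24%; the attrition allowance is 30%. If losses are independent with retention q, the chance of equal arms is the sum over k of [C(29,k) q^k (1 − q)^(29−k)]². This is 0.123 at q = 0.76 and 0.114 at q = 0.70.

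**The case against.** The strongest reply is that the declared primary outcomes are not touched. Under Primary outcomes: "The primary outcomes are the differences in the number of subjects that will lose at least 50% of excess weight", together with the number whose HbA1c is below 5.7%. Both are binary and go to the chi-square test. This stands. A reader might infer that the primary analysis is invalid, but the document does not support that for the outcomes as defined there.

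Second, a reader might infer that paired tests inflate false positives. With random pairing they do not. A type I error of 62% arose only when both arms were sorted by the outcome before pairing, and nothing in the article suggests that would be done.

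Third, the authors may have meant within-arm change. The sentence says otherwise, and that reading would still leave no test between arms. It would be too strong, however, to say that nothing would compare probiotic with placebo: weighted mean differences and Cohen's d are mentioned, so between-arm estimates are plausibly planned. It would also be too strong to say that every within-arm test must be significant because of the surgery. The figures support that only for weight measured from before surgery. At the average weight and height under Recruitment status, excess weight is 129.7 − 25 × 1.70² = 57.45 kg, half of which is about 28.7 kg. Those are means of the 14 participants enrolled so far. Supplementation starts at 3 months, so a before/after test could equally start there.

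An unseen analysis plan does not dispose of the point, because the article states an unsuitable test rather than omitting one. Stratified blocks do not help either: they balance numbers within HbA1c strata and create no one-to-one pairs.

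**Conclusion.** The point holds for continuous outcomes: the named tests do not fit the design, and no suitable test is named elsewhere in the article. Followed literally, the plan gives a p-value that depends on an arbitrary pairing, or requires participants without a partner to be discarded. It does not imply inflated type I error or a large loss of power, and it leaves the binary primary outcomes alone.

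It must still be corrected, because excess weight loss and HbA1c appear as continuous measures in the primary aims, and excess weight loss and glucose determined the sample size. The simulated percentages assume normal data, equal SDs, 22 per arm and a two-sided 0.05 level. The 11–12% chance of equal arms assumes independent losses of 24–30%.

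**What to change.** In the Statistical analysis section, replace the sentence naming the paired tests. For comparisons between arms, name the independent-samples (Welch) t-test and, for non-normal data, the Mann-Whitney test. A linear model with arm, baseline value and HbA1c stratum is a reasonable option but is not needed to cure the error. State that the paired t-test and Wilcoxon signed rank test are used only to describe change within an arm. The cost is one or two sentences, in an amendment or the analysis plan, before the data are analysed. No new data, visits or participants are needed.
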